## Methods

A two-armed RCT will be conducted, in which participants will be randomly allocated to (1) the PLACES intervention group or (2) the CAU control group. Participant recruitment, intervention delivery, and measurement timing are shown in Fig. 1. Participants will receive questionnaires at baseline (T0) and after 3 (T1), 6 (T2), and 12 months (T3) follow-up. The participant flowchart is shown in Fig. 2. The “Standard Protocol Items: Recommendations for Interventional Trials” (SPIRIT) 2013 statement was used to structure the design of this study [26] (Appendix S1). In addition to the trial registration (NCT06028048), all items of the World Health Organization Trial Registration Data Set are outlined in Appendix S2.

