### Secondary outcome measures

Secondary outcome measures will include:Time until paid employment, defined as the number of days between randomization and starting paid employment. To calculate this, participants will be asked about the date they started their new jobChange in working hours (if employed), measured by comparing the average numbers of hours worked weekly at different times of follow-up. For each work situation (e.g., part-time, voluntary), participants will be asked about the number of hours per week they work. The hours worked in paid employment will be used for the analysesHealth-related quality of life, measured using the Short Form-12 (SF-12), which includes the subscales vitality, physical functioning, bodily pain, general health perceptions, and physical role functioning [32]. For the economic evaluation, the participants’ SF-12 health states will be converted to utility values, ranging from 0 (quality of life equal to death) to 1 (quality of life equal to optimal health), using the tariff of Brazier et al. [33]. Then, quality-adjusted life years (QALYs) will be estimated using the “area under the curve approach”Quality of working life, measured with the 23-item Cancer-specific Quality of Working Life Questionnaire (QWLQ-CS), which comprises five subscales: (1) meaning of work, (2) perception of the work situation, (3) atmosphere in the work environment, (4) understanding and recognition in the organization, and (5) problems due to the health situation [34]Work ability, assessed with a single question of the Work Ability Index (WAI), asking participants to estimate their current work ability compared with their lifetime best (0, cannot work at all; 10, work ability at its best) [35]Self-efficacy regarding RTW, measured using the 11-item self-efficacy scale [29]Type of paid employment, defined by the work situation. This will be reported with descriptive statistics. Answer options are as follows: fulltime, part-time, self-employed, studying, retired, involuntarily unemployed, voluntarily unemployed, partially or fully work-disabled, employed but on sick leave, unemployed and on sick leave, household/caring for others, and “other”

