### Effect evaluation

To evaluate the effectiveness of the PLACES intervention compared to CAU at different time points, mixed-effect regression (either linear or logistic regression) with participant as a random intercept will be conducted. Since we stratified for “received social benefit” and the “labor region,” they will be included as covariates in the model. In all models, the main independent variable will be group allocation (i.e., intervention or control group), and both unadjusted and adjusted models will be presented. Additionally, the influence of time (T1, T2, T3) on the intervention’s effect will be examined (group*time interaction effect). The adjusted models will include potential confounders, such as age, gender, time since diagnosis, type of cancer, type of treatment, importance of work, RTW expectation [15, 38], and baseline value of the dependent variable.

In addition, subgroup analyses will be performed for gender (i.e., male, female or other) time since diagnosis (i.e., ≤ 3 years, > 3 years), type of cancer diagnosis (i.e., breast, colon or other), and type of treatment (i.e., locoregional therapy, systemic therapy or multimodal treatment). All analyses will be performed on an intention-to-treat basis. Per-protocol analyses will be carried out comparing participants in the intervention group who completed at least phase 1 of the intervention and had at least one meeting in phase 2 of the intervention, to participants in the control group.

We will use mixed-effects logistic regression to assess the primary outcome, paid employment [yes/no] at T1, T2, and T3. Odds ratios (ORs) with corresponding 95% confidence intervals (CIs) will be calculated to examine the effect of the intervention on the odds of paid employment.

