### Cost effectiveness evaluation

The cost-utility analysis, in terms of QALYs, will be performed from the occupational healthcare perspective. Additionally, an ROI analysis will be conducted from the SSA perspective. For the cost-utility analysis, an incremental cost-effectiveness ratio (ICER) will be estimated by dividing the difference in occupational health costs between groups (∆C) by the corresponding difference in effects (∆E): (ICER = ∆C/∆E). To graphically illustrate the uncertainty surrounding the ICER, a cost-effectiveness plane (CE-plane) and a cost-effectiveness acceptability curve (CEAC) will be plotted. The ROI analysis will be conducted according to the recommendations of van Dongen and colleagues [41]. Various sensitivity analyses will be conducted to assess the robustness of the results (e.g., complete-case analysis).

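### The economic section states no adjustment for baseline utility in the QALY difference that enters the ICER

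*Protocol article*

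**What the plan says.** All of the following is from the protocol article.

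- **Secondary outcome measures.** For the economic evaluation, "the participants’ SF-12 health states will be converted to utility values, ranging from 0" (death) to 1 (optimal health). After that, "quality-adjusted life years (QALYs) will be estimated using the" area under the curve.
- **Methods.** "Participants will receive questionnaires at baseline (T0) and after 3 (T1), 6 (T2), and 12 months (T3) follow-up".
- **Cost effectiveness evaluation.** The ICER comes from "dividing the difference in occupational health costs between groups" "by the corresponding difference in effects". A CE-plane and a CEAC show the uncertainty. On robustness: "Various sensitivity analyses will be conducted to assess the robustness of the results (e.g., complete-case analysis"). No covariate is named in this section.
- **Effect evaluation.** Both unadjusted and adjusted models are planned. The adjusted models list potential confounders that end with "importance of work, RTW expectation [15, 38], and baseline value of the dependent variable".
- **Randomization.** Allocation is 1:1, stratified by region and social benefit type. Baseline utility is not a stratification factor.

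**The concern.** A 12-month area under the utility curve contains the T0 utility itself, and later utilities are correlated with it. An arm that happens to start with better utility will therefore tend to show more QALYs even if the intervention does nothing. Stratification does not guard against this, because utility is not a stratification factor.

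The rule under Effect evaluation adjusts for the "baseline value of the dependent variable". A QALY accrued over 12 months has no baseline value of its own, so the rule does not say that T0 utility is the covariate. That section also keeps both adjusted and unadjusted models, and nothing says which of the two would feed the ICER.

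Cost-effectiveness is one of the two questions that the trial sets itself, while the sample size rests on paid employment alone. Precision for the QALY difference is therefore not planned for, and avoidable noise in the ICER denominator matters. Leaving the choice open also allows it to be made after the results are seen.

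**Working it through.** The article gives no figure for utilities, QALYs or the ICER, so there is no stated figure to reproduce.

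**Inputs from the article.** Visits at 0, 0.25, 0.5 and 1 year; 82 participants per arm; QALY by area under the curve.

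**Assumptions, because the article gives neither figure.** Utility SD of 0.10 to 0.15, equal at all visits. The same correlation rho between any two visits (compound symmetry), with rho from 0.3 to 0.7.

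**Step 1: trapezium weights.**
- T0: 0.25/2 = 0.125
- T1: 0.5/2 = 0.25
- T2: (1 − 0.25)/2 = 0.375
- T3: (1 − 0.5)/2 = 0.25

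They sum to 1.

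**Step 2: carry-over of a baseline difference.** The expected share of a T0 difference that appears in an unadjusted QALY difference is b = 0.125 + 0.875·rho. The first term is the direct weight of T0, and the second is persistence into T1 to T3.

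**Step 3: variance removed by adjustment.** In units of SD², the QALY variance is V = (1 − rho)·Σw² + rho, with Σw² = 0.015625 + 0.0625 + 0.140625 + 0.0625 = 0.28125. The share explained by T0 utility is b²/V.

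| rho | b | V | b²/V | SE ratio, √(1 − b²/V) |
|---|---|---|---|---|
| 0.3 | 0.388 | 0.497 | 0.30 | 0.84 |
| 0.5 | 0.562 | 0.641 | 0.49 | 0.71 |
| 0.7 | 0.737 | 0.784 | 0.69 | 0.55 |

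**Step 4: size of a chance imbalance.** The SE of the T0 difference is SD·√(2/82), which is 0.016 at SD 0.10 and 0.023 at SD 0.15.
- A one-SE imbalance shifts the QALY difference by 0.006 (SD 0.10, rho 0.3) to 0.017 (SD 0.15, rho 0.7). Only 0.002 to 0.003 of this is the direct T0 weight.
- A 1.96-SE imbalance shifts it by 0.012 to 0.034.

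**Step 5: precision.** The SE of the QALY difference is SD·√(2V/82) without adjustment, and that value times the SE ratio with it.
- SD 0.10: from 0.0110 to 0.0092 at rho 0.3, and from 0.0138 to 0.0077 at rho 0.7.
- SD 0.15: from 0.0165 to 0.0138 at rho 0.3, and from 0.0207 to 0.0115 at rho 0.7.

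**The case against.** The strongest reply is that the article nowhere prescribes a raw difference. The ICER formula is a definition and holds equally for raw and adjusted differences. A journal article condenses a fuller plan, and the economic section looks abridged: it offers complete-case analysis as a sensitivity analysis without describing the main handling of missing data, and net monetary benefit is in the abbreviation list but not in the text. The Effect evaluation section shows that the authors do plan baseline adjustment, and the natural baseline for a utility-based QALY is T0 utility.

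Much of this stands. A reader might infer that the plan fixes a plain, unadjusted comparison, but the estimator is simply not named. A reader might also infer that a baseline difference enters the ICER in full; the carry-over is partial. Nor is this systematic bias: over repeated randomizations the unadjusted difference is unbiased, and correctly computed uncertainty already includes the extra variance.

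What does not fall away is that the article spells out covariate adjustment for the effect outcomes, gives the economic analysis its own section with none, and does not link the two. Even if the effect-model rule were extended to QALYs, it would leave both an adjusted and an unadjusted result without saying which enters the ICER. Adjustment is also a better estimator that uses data already planned, so the point goes beyond a missing definition.

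**Conclusion.** The point holds as a recommendation to state the adjustment, not as a demonstrated error. Computed as written and without adjustment, the QALY difference would carry about 0.39 to 0.74 of any chance T0 utility difference. It would also have an SE about 1.2 to 1.8 times the adjusted one (1/0.84 to 1/0.55). The harm is lost precision and conditional bias.

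The carry-over and the variance shares rest on the assumed rho, equal SDs and compound symmetry. The shifts in QALYs rest in addition on the assumed SD of 0.10 to 0.15. The calculation also takes the SF-12 to be part of the T0 questionnaire. A 12-month area under the curve requires this, but the available text does not list the SF-12 by visit and the schedule figure is not shown.

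A reader might infer that chance imbalance will decide the sign of the ICER. The article gives no expected QALY difference, so that cannot be shown. It is a possibility only if the true difference is close to zero.

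**What to change.** Add to Cost effectiveness evaluation: the QALY difference used in the ICER, the CE-plane and the CEAC is estimated by regression of QALYs on arm, T0 utility and the two stratification factors (social benefit type and region), with the unadjusted difference reported as a sensitivity analysis.

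A joint model for costs and effects, such as seemingly unrelated regression, is one acceptable way to do this but is not required. If a fuller plan already specifies the adjustment, a cross-reference is enough.

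The cost is one sentence, settled before the data are analysed. No new data are needed, provided that the SF-12 is collected at T0.

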#### Costs

A cost-utility analysis (CUA) will be performed from an occupational healthcare perspective. The occupational healthcare perspective includes all costs associated with the formal Dutch occupational healthcare sector; i.e., intervention costs, occupational healthcare costs, absenteeism costs, and presenteeism costs. Intervention costs will be determined using a micro-costing approach. This means that detailed data will be collected about the number of resources used for developing, implementing, and delivering the intervention, which will in turn be valued using their respective unit prices. Occupational healthcare costs for all participants will be measured through self-reported questionnaires regarding the participant’s use of occupational healthcare services (e.g., insurance physician, labor expert), which will also be valued using prices of professional organizations. Absenteeism and presenteeism costs will be measured using the self-reported iMTA Productivity Costs Questionnaire (iPCQ) [36] and will be valued using gender-specific price weights [31]. The return on investment analysis (ROI) will be performed from the payer perspective. The costs for the payer perspective include the costs made by the SSA to provide the intervention, including the difference in costs for the intervention between the intervention and control group. Benefits will be defined as the mean difference in benefits costs. Information on the individuals’ benefits costs will be derived from the self-reported questionnaires and information about employment status.

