**Discussion:**

We hypothesize that the PLACES intervention will be effective in obtaining paid employment, enhancing work ability, and improving quality of life. In addition, we expect the intervention to be cost-effective. If proven effective and cost-effective, actions should be taken to implement the intervention in usual care.

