In addition to these organizational adjustments of the IPS principles, the content of the PLACES intervention was tailored to the needs and preferences of unemployed and/or work-disabled cancer survivors. This was based on a systematic review [19] and focus group interviews ([name] et al. in preparation) with cancer survivors who had engaged in job-seeking activities for paid employment in the 2 years prior to the study (from a situation of unemployment or work disability). The review on interventions aimed at enhancing the work participation of cancer survivors [19], advocated, among others, for inclusion of the workplace even for individuals without an employment contract who are re-entering the labor market. This is in line with the principles of IPS on systematic job development and time-unlimited individualized support and resulted in the emphasis of support on the job and involvement of the employer during the intervention. The focus group interviews provided insight into facilitators and barriers encountered during the process of reintegration after cancer as well as the cancer survivors’ met and unmet needs throughout the reintegration process ([name] et al. in preparation). The insights gained from these interviews were used to formulate explicit recommendations for the coaches who perform the intervention, such as guidelines regarding the frequency and nature of the meetings. The specific guidelines for each phase of the intervention can be found in the content of the intervention and Fig. 3.

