**Cost-effectiveness measures**			
Social benefits	1	Social benefit received by participant categorized as sickness benefit, partial or full work disability benefit	Categorical
Intervention costs		The costs of the reintegration trajectories at the SSA are equal to the sum of 67 h × hourly rate × number of participants. The cost of each individual trajectory is the same	Continuous
Productivity^c^	4	iMTA Productivity Costs Questionnaire (iPCQ) measures productivity costs related to health conditions, capturing absenteeism, presenteeism and performance at work (49)	Continuous
Occupational healthcare consumption	1	An Adapted iMTA Medical Costs Questionnaire (IMTQ) will assess self-reported occupational healthcare consumption categorized by different professionals (e.g., labor expert, reintegration services, physical therapist) and the number of appointment with each professional (50)	Continuous

^a^Used as potential confounder

^b^Used for subgroup analyses

^c^Only completed by participants with employment

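### The protocol defines the cost-utility analysis's intervention cost in two incompatible ways, and one of them lets one-off development cost into the ICER

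*Protocol article*

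**What the plan says.** The Costs section sets an occupational healthcare perspective for the cost-utility analysis and lists what it contains: "intervention costs, occupational healthcare costs, absenteeism costs, and presenteeism costs". It then fixes the method: "Intervention costs will be determined using a micro-costing approach". It spells this out by saying that "detailed data will be collected about the number of resources used for developing, implementing, and delivering the intervention", with unit prices applied to those resources.

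Table 2, under the cost-effectiveness measures, has its own row for intervention costs. There, the costs of the SSA's reintegration trajectories "are equal to the sum of 67 h × hourly rate × number of participants", followed by "The cost of each individual trajectory is the same". Neither development nor implementation appears.

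The section on the cost-effectiveness evaluation forms the ICER by "dividing the difference in occupational health costs between groups (∆C) by the corresponding difference in effects (∆E"). The Discussion paragraph of the abstract says what a favourable result is for: if PLACES proves effective and cost-effective, "actions should be taken to implement the intervention in usual care". On how the content was tailored to cancer survivors, the Development section says: "This was based on a systematic review [19] and focus group interviews".

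The return-on-investment analysis is described separately, from the payer's side. Its cost is what the SSA spends on providing the intervention; development is not named.

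**The concern.** Two definitions of one input give two values of the cost difference, and the article does not say which one the cost-utility analysis will use.

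The broader definition also fits the stated purpose poorly. Development is a one-off expense, already incurred by the time anyone decides on adoption. It does not grow with the number of people served and would not be paid again if PLACES became usual care. The comparator has no matching item: occupational healthcare services are valued at professional bodies' prices, and no separate charge is made for having designed them. An ICER that includes development therefore answers what this project cost historically, rather than what adopting the programme would cost.

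At stake is the interpretation of the cost-utility result. Cost-effectiveness is one of the two aims given at the end of the Background.

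**Working it through.** **1. The two definitions side by side.**

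| Component | Costs section | Table 2 |
|---|---|---|
| Development | included | absent |
| Implementation | included | absent |
| Delivery | resources used, by micro-costing | fixed at 67 h × rate for everyone |

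The two differ even on delivery. The section on the content of the intervention gives 67 hours as a maximum per participant, and Table 3 has coaches log the hours they actually spend. Micro-costing could use those logged hours; Table 2 charges the maximum to all.

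**2. Route into the ICER.** Let D be the development cost, N the number of people it is spread over, and ΔQALY the difference in effect.

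- Under Table 2, the development load on ΔC is 0.
- Under the Costs section, the load per intervention participant is D/N.
- The shift in the ICER is (D/N)/ΔQALY. D cannot be negative, so ΔC can only rise; with a positive ΔQALY, so does the ICER.

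**3. What the article supplies.** It gives 67 hours and an intervention arm of 82. It gives no D, hourly rate, ΔQALY or N. There is thus no cost figure of the plan's own to reproduce, and every euro and QALY value below is an assumption.

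**4. Load if D were spread over the 82 intervention participants (N = 82).**

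- D = EUR 25,000: 25,000/82 = EUR 305
- D = EUR 50,000: 50,000/82 = EUR 610
- D = EUR 100,000: 100,000/82 = EUR 1,220
- D = EUR 200,000: 200,000/82 = EUR 2,439

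At an assumed EUR 60–120 per hour, Table 2's delivery cost is 67 × 60 = EUR 4,020 to 67 × 120 = EUR 8,040 per participant. The load then runs from 305/8,040 = 4% to 2,439/4,020 = 61% of delivery cost.

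**5. Shift in the ICER for D = EUR 50,000.**

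| Spread over | Load per person | ΔQALY 0.02 | ΔQALY 0.05 |
|---|---|---|---|
| 82 participants | EUR 610 | about EUR 30,500 per QALY | about EUR 12,200 per QALY |
| 1,000 users (assumed) | EUR 50 | EUR 2,500 per QALY | EUR 1,000 per QALY |

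**6. Dependence on the denominator.** With N equal to the arm size, doubling the arm to 164 halves the load: 50,000/164 = EUR 305. The programme would be the same, and only enrolment would have changed. Under an expected-users denominator this artefact disappears and the load may be negligible.

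**The case against.** A reader might infer that the plan has settled on charging the whole development cost to the trial's 82 intervention participants. The article does not support that. It says that development resources will be recorded and valued; it does not say how they will be allocated. Dividing by 82 is a natural default in a comparison of trial arms, but it is an inference, and Table 2 would put the load at zero.

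Two further inferences also go too far. The review and focus groups are described as sources for the intervention's content, and nothing says that they will be costed; the perspective is confined to the formal occupational healthcare sector. Nor can the point be carried over to the whole adoption case, because the SSA's position has its own analysis, costed on what the SSA pays to provide PLACES.

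It can also be said that Table 2 describes only the SSA trajectory cost for the return-on-investment analysis, that a condensed article may leave allocation rules to a fuller plan, and that the sensitivity analyses are promised in general terms, with complete-case only as an example. These arguments limit the point but do not remove it. Table 2 labels its row as intervention costs without restricting it to one analysis. The inclusion of development is a stated costing rule, not an omitted detail. No named analysis would show the ICER without it.

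**Conclusion.** The point holds as a contradiction between the Costs section and Table 2, with a known direction and an unknown size. If the Costs section governs, the cost-utility analysis includes an expense irrelevant to adoption in usual care, and PLACES looks more costly than it would be to adopt. If Table 2 governs, there is no development load, but implementation cost is missing too and delivery is charged at the ceiling.

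The illustrative range is wide: EUR 610 or EUR 50 per person for the same assumed EUR 50,000, depending only on the denominator. It should not be read as an estimate of bias. The conclusion rests on a literal reading of the Costs section and on taking implementation in usual care as the decision that the ICER serves.

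The severity is minor to moderate. The primary outcome and its analysis are untouched, and the return-on-investment analysis is not shown to be affected.

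**What to change.** Reconcile the Costs section and Table 2 to one definition of intervention cost for the cost-utility analysis. If the Table 2 formula is meant only for the return-on-investment analysis, say so in the table, and state whether delivery is costed at logged hours or at a flat 67.

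Base the main ICER on recurring implementation and delivery costs. Report development cost as a separate line, and add one sensitivity analysis that includes it, spread over a stated expected number of users rather than over the trial arm.

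This needs wording only, because the component data are already to be collected. The downside is that the base case no longer shows the full historical cost; the separate line and the sensitivity analysis restore it.
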